## **Methods**

### *Context*

These hypotheses will be tested with data from the PEPaNIC trial. A total of 1440 children from three large tertiary referral PICUs in three different countries (KU Leuven in Belgium, Erasmus MC in The Netherlands and Stollery Children's Hospital in Canada) were randomly assigned to late PN (Late PN; intervention) or early PN (Early PN; standard care). Initiation and incline of enteral nutrition and administration of trace elements, minerals and vitamins were identical in both groups. Patients assigned to the late PN group (n=717) received no PN at all during the first week of critical illness. Patients in the early PN group (n=723) received PN within 24 hours after admission to supplement insufficient enteral nutrition. After the first week,

PN was administered equally in both groups according to standard nutritional protocol if enteral nutrition was insufficient to meet nutritional goals. The full study protocol and clinical outcomes have been reported in detail elsewhere.

#### *Data collection and definitions*

Data on patient characteristics, outcome measurements and parameters for nutritional status were prospectively collected and registered in the study database. Since multiple measurements of weight and height were not performed for the Belgian and Canadian patients, we will exclude these patients for the analyses concerning change in weight during PICU stay.

The nutritional status will be defined based on WFA in children younger than one year and BMI-for-age (BFA) in children older than one year. Acute undernutrition is defined as WFA or BFA SD scores  $<-2$ . Country specific reference values for WFA and BFA will be used to calculate SD scores, if possible. If these are unavailable, WHO reference values will be used.

#### *Outcomes*

Primary outcomes are incidence of new infections and duration of PICU dependency, which will be reported as the crude number of PICU days and as the time to live discharge from the PICU, to account for mortality as a competing risk.

Secondary outcomes are duration of mechanical ventilation (and time to life weaning from mechanical ventilation), duration of hospital stay (and time to life discharge from the hospital), and the safety outcomes 7-day mortality (i.e. during the intervention period), 90-day mortality and hypoglycemia during the first week.

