#### *Statistical analyses*

As the sample size of the present study depended on the number of undernourished children included in the PEPaNIC-trial, we plan to perform a retrospective power analysis based on observed differences for risk of new infection as primary endpoint, rather than performing an a priori sample size calculation.

Variables will be reported as percentages, means ( $\pm$ SD) if normally distributed or as medians (IQR) if not-normally distributed. Change in weight will be reported as change in WFA or BFA SD score. Proportions will be analyzed univariably using chi-square test, means with t-test and medians with Mann Whitney test. The time-to-event effect sizes will be estimated with use of Cox proportional-hazard analysis, with data censored at 90 days. To take into account death as a competing risk for outcomes related to duration of care, data for non-survivors will be censored at 91 days. These time-to-event outcomes will be analyzed adjusted for baseline risk factors treatment center, age, diagnosis group, STRONGkids category, PIM2 score and PELOD score. The multivariable analysis of the effect of the intervention on dichotomized outcomes, adjusted for baseline risk factors, will be performed using logistic regression. Analyses regarding change in weight will additionally be adjusted for malnourishment upon admission.

P-values  $\leq 0.05$  will be considered statistically significant. P-values for interaction were calculated with the use of multivariable logistic regression analyses and multivariable Cox proportional-hazard analyses with a threshold for significance of interaction set at  $P \leq 0.10$ .

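### The SAP gives the primary outcome of PICU duration two forms, crude days and time to live discharge, each tested at the 5% level, and does not say which one decides

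*Supplement*

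**What the plan says.** The Outcomes section of the SAP lists two primary outcomes, new infections and duration of PICU dependency. The second is to appear in two forms, "which will be reported as the crude number of PICU days and as the time to live discharge from the PICU", and the reason given for the live-discharge form is "to account for mortality as a competing risk". The secondary duration outcomes are paired in the same way: "duration of mechanical ventilation (and time to life weaning from mechanical ventilation), duration of hospital stay (and time to life discharge from the hospital").

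The Statistical analyses section supplies the tests:

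- Summaries of continuous variables are compared univariably: "means with t-test and medians with Mann Whitney test".
- For event times, "The time-to-event effect sizes will be estimated with use of Cox proportional-hazard analysis, with data censored at 90 days".
- Deaths are dealt with as follows: "To take into account death as a competing risk for outcomes related to duration of care, data for non-survivors will be censored at 91 days".
- Adjustment is stated for the event-time form ("These time-to-event outcomes will be analyzed adjusted for baseline risk factors treatment center, age, diagnosis group" and further covariates) and for dichotomised outcomes. None is stated for crude days.

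One threshold, P≤0.05, covers every main comparison. The SAP does not rank the two forms or say what follows if they disagree.

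The final protocol does choose for the main trial. Sections 18.1.1 and 20.2 analyse time to discharge alive by Cox regression and only describe actual stay, split into ICU survivors and non-survivors.

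**The concern.** The SAP hypothesis under Aims and hypotheses is a shorter PICU stay with late PN in undernourished children. Either form could be cited in support of it. With two tests and no stated order, the chance of a false positive on this one outcome exceeds 5%.

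The two forms also treat death differently. Setting non-survivors to day 91 is a censoring instruction, which has meaning only in a time-to-event analysis. In crude days, a child who dies on day 2 has a two-day stay and ranks better than a survivor who leaves on day 5. If mortality differs between the arms, the two forms answer different questions, and the plan gives no rule for reading a split result.

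**Working it through.** **Plan's own figure.** The SAP gives no power or error figure for PICU duration, so there is none to reproduce on this point. The protocol's fully specified figure concerns infections (20% versus 15%, 720 per arm). It reproduces at 80.3% one-tailed and 70.5% two-tailed, against a stated 80% and 70%, but does not bear on the choice between the two duration forms.

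**Inputs from the documents.**

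- PICU stay: median 3 days, mean 5.5 days (Leuven, final protocol section 15.1).
- Trial size: 1440.
- Undernutrition prevalence: up to 24% (SAP Background).
- Significance threshold: P≤0.05.
- Deaths censored at day 91, other data at day 90.

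**Assumptions, because the documents do not give them.**

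- Undernourished share of 10–24%, which gives 0.10 × 1440 / 2 = 72 to 0.24 × 1440 / 2 ≈ 173 per arm.
- Mortality of 6% in both arms, or 8% (late) versus 4% (early).
- Time to death exponential with a mean of 2 or 5 days.

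**Model.** Survivors' stay is log-normal, exp(ln 3 + s·Z), with s = √(2 ln(5.5/3)) = 1.10. Crude days are compared by Mann-Whitney in all children. Live discharge is compared by the log-rank test (the score test of the unadjusted Cox model), with deaths at day 91 and administrative censoring at day 90. Each setting has 2000 simulated trials. Ranges run over both arm sizes and both death timings, and over repeat runs.

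**Step 1: no true difference.** Two independent 5% tests would give 1 − 0.95² = 9.75%, which serves as a reference ceiling.

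| Mortality, both arms | At least one form significant |
|---|---|
| 6% | about 8–9% |
| 0% | about 6–8% |

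The inflation is larger with deaths because deaths weaken the correlation between the two tests.

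**Step 2: mortality 8% (late) versus 4% (early), survivors' stay identical.**

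| Form | Significant |
|---|---|
| Crude days | about 4–6% |
| Time to live discharge | about 11–21% |

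Crude days stay at about their nominal level and miss the loss.

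**Step 3: late-arm survivors' stay 20% shorter.**

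| Mortality, late versus early | Crude days significant |
|---|---|
| 8% versus 4% | about 18–51% |
| 6% versus 6% | about 19–42% |
| 0% versus 0% | about 22–45% |

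The crude-day result hardly depends on the deaths. It comes mostly from the real reduction in stay that was put in. In the 8% versus 4% row, live discharge is significant in only about 4–6%, because the shorter stay and the extra deaths offset each other.

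**Step 4: both forms significant in opposite directions.** At 72–173 per arm and 8% versus 4% this happens in at most 0.3% of trials. In a separate set of runs (log-SD from the interquartile range of 2–6 days, deaths at a median of day 2, identical survivor stay), it occurs in 1% at 100 per arm with 15% versus 5% mortality. It reaches 19% only at 720 per arm with the same mortality contrast.

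**The case against.** The SAP says the two forms will be reported. That crude days will be tested, and tested with survivors and non-survivors pooled, is inferred from the general rule for means and medians. The SAP also hints at a preference. Live discharge is the form introduced to deal with death, and both the death rule and the covariate adjustment attach to it. The SAP refers readers to the full trial protocol, which does choose. The SAP makes 7-day and 90-day mortality outcomes too, so an excess of deaths would be seen beside any difference in crude days. Finally, this is a declared secondary analysis in a programme whose protocol states that it does not correct for multiple testing.

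Most of this is fair, and it limits the size of the problem. It does not supply the missing statement. A hint of preference is no decision rule, and the protocol's choice concerns the main trial and is not carried into the SAP's own definition of its primary outcome. A policy of not correcting across endpoints also leaves open which of two versions of one endpoint is the endpoint.

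Two stronger readings should be resisted. A reader might infer that the two forms will tend to give opposite answers; Step 4 shows that two significant results in opposite directions need a large excess of early deaths. A reader might also infer that more deaths would produce a false crude-day benefit; Step 2 shows that doubled mortality alone barely moves the crude test at these sizes.

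**Conclusion.** The point stands as a missing decision rule on a primary outcome and should be corrected. Leaving both forms in place raises the false-positive chance for this outcome by roughly 3 to 4 percentage points at the assumed 6% mortality, and by 1 to 3 points if nobody dies. When mortality differs, the main risk is a split result, and the crude-day form is the one that fails to register the harm. These sizes rest on assumed mortality, timing of death and subgroup size, and on a log-normal stay fitted to one centre's figures for all its admissions. The absence of a named deciding form, and the fact that the death rule cannot reach crude days, depend on none of those assumptions.

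**What to change.** In the SAP Outcomes section, state that time to live discharge from the PICU (Cox regression, non-survivors censored at 91 days) is the deciding measure of PICU dependency. State that crude PICU days are descriptive, shown separately for survivors and non-survivors, without a significance test. Apply the same rule to mechanical ventilation (time to live weaning) and hospital stay (time to live discharge). This follows final protocol sections 18.1.1 and 20.2.

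The cost is a sentence or two. No new data, extra patients or additional modelling are needed. The small loss is the p-value for crude days.

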#### *Statistical analyses*

As the sample size of the present study depended on the number of undernourished children included in the PEPaNIC-trial, we plan to perform a retrospective power analysis based on observed differences for risk of new infection as primary endpoint, rather than performing an a priori sample size calculation.

Variables will be reported as percentages, means ( $\pm$ SD) if normally distributed or as medians (IQR) if not-normally distributed. Change in weight will be reported as change in WFA or BFA SD score. Proportions will be analyzed univariably using chi-square test, means with t-test and medians with Mann Whitney test. The time-to-event effect sizes will be estimated with use of Cox proportional-hazard analysis, with data censored at 90 days. To take into account death as a competing risk for outcomes related to duration of care, data for non-survivors will be censored at 91 days. These time-to-event outcomes will be analyzed adjusted for baseline risk factors treatment center, age, diagnosis group, STRONGkids category, PIM2 score and PELOD score. The multivariable analysis of the effect of the intervention on dichotomized outcomes, adjusted for baseline risk factors, will be performed using logistic regression. Analyses regarding change in weight will additionally be adjusted for malnourishment upon admission.

P-values  $\leq 0.05$  will be considered statistically significant. P-values for interaction were calculated with the use of multivariable logistic regression analyses and multivariable Cox proportional-hazard analyses with a threshold for significance of interaction set at  $P \leq 0.10$ .

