In our study we aim to evaluate whether the current practice of Early PN in critically ill children really provides clinical benefits over a strategy of withholding PN during the first 7 days in the paediatric ICU. The evaluation will be done in a multicentre randomized controlled trial performed in three large expert tertiary referral paediatric ICUs. The study will be statistically sufficiently powered to detect differences in clinically relevant outcome variables (the rate of new infections and the length of stay in the ICU). The trial will also be able to detect a doubling or halving of the mortality rate with a respectable statistical power (details on statistical power are given in the description further on). The results of this randomized controlled trial will provide, for the first time, high quality evidence for practice guidelines for nutrition in critically ill children. It will answer the question whether Early PN is beneficial, harmful or neutral in comparison with the new therapy

of withholding PN during the first week of critical illness. In weighing this evidence for current nutritional practice, this study will take into account 1) the short-term as well as the long-term health effects of the feeding protocols, 2) costs, and cost-effectiveness and 3) some insights into the underlying mechanisms of the observed clinical differences.

Also, one of the goals of the PEPaNIC study is to look into the tolerance for enteral nutrition (EN). In critically ill children EN is preferred because it is more physiological, presents fewer complications, leads to a better outcome and is less expensive than PN. However, EN often fails in this patient group due to impaired gastrointestinal (GI) motility, digestion and absorption following ischemia, inflammation or starvation leading to intolerance to EN. To improve future EN tolerance in critically ill children we have to gain insight in parameters of influence in this complex process.

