### **15.4 Sample size calculation**

The sample size (N=1440, 720 per arm) is calculated in order to detect, with at least 80% power (one-tailed; the two-tailed power is 70%) and 95% certainty, a reduction in PICU infections from 20% to 15% and, with at least 90% power (two-tailed) and 95% certainty, a reduction in mean duration of stay in PICU of 1 day. With this sample size, and for safety reasons, also any substantial impact on mortality (increase or decrease with an absolute +/- 2%, although unexpected taken the adult data), can be excluded with a power of around 62-75% depending on the true mortality in the total population. We plan to calculate the true power of the study for detection of any eventual smaller differences in these outcomes.

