## **Background**

The prevalence of undernutrition in children who are admitted to the Pediatric Intensive Care Unit (PICU) is up to 24%. Undernutrition on admission is associated with increased mortality and morbidity such as infectious complications, longer need for mechanical ventilation and prolonged hospital stay.

Hulst et al showed that the nutritional status of children admitted to the PICU declined from admission to discharge from the PICU and that these children showed catch-up growth within 6 months. Both protein intake of at least 2.3 mg/kg/day during PICU stay and higher enteral caloric intake after PICU stay have been associated with an increase in weight-for-age (WFA) SD score in subgroups of children. However, this association could not be found for duration of parenteral nutrition (PN). Furthermore, it is unknown if deterioration of nutritional status during PICU stay independently impairs clinical outcome.

The PEPaNIC trial in 1440 critically ill children showed that withholding PN for one week resulted in fewer new infections and reduced the duration of PICU stay as compared with early initiation of PN. These clinical benefits were even larger in children who were at high risk of undernutrition as reflected by a high score on the Screening Tool for Risk on Nutritional status and Growth (STRONGkids). However, the STRONGkids score has originally been developed for children admitted to the pediatric ward, not children admitted to the PICU. The effect of late initiation of PN in children who were undernourished upon admission has not yet been evaluated.

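### 7-day mortality in undernourished children: ordinary logistic regression with about 11 to 20 coefficients may meet no more deaths than that; a Firth fit of the same covariates would be more accurate at little cost

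*Supplement*

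**What the plan says.** The SAP plans a secondary analysis whose first aim is the effect of late PN in children undernourished on admission. Under Outcomes it lists "the safety outcomes 7-day mortality (i.e. during the intervention period), 90-day mortality and hypoglycemia during the first week".

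Under Statistical analyses:
- Unadjusted: "Proportions will be analyzed univariably using chi-square test".
- Adjusted: "The multivariable analysis of the effect of the intervention on dichotomized outcomes, adjusted for baseline risk factors, will be performed using logistic regression".
- The only list of such factors is in the preceding sentence, on time-to-event outcomes: "baseline risk factors treatment center, age, diagnosis group, STRONGkids category, PIM2 score and PELOD score".
- Interaction: "P-values for interaction were calculated with the use of multivariable logistic regression analyses and multivariable Cox proportional-hazard analyses".

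No penalised or exact fit, reduced covariate set or rule for sparse events is named. Neither document states how many children were undernourished or how many of them died within 7 days.

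**The concern.** One model is prescribed for all binary outcomes, from infections, which are common, to early death, which is not. Maximum-likelihood logistic regression behaves poorly when events are about as few as coefficients: estimates become noisy, drift away from no effect when a true effect exists, and can be infinite.

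At stake is the adjusted odds ratio for early death when nutrition is withheld from undernourished children. A noisier figure than necessary can be over-read in either direction.

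**Working it through.** **1. Coefficients (intercept excluded).** Treatment 1, centre 2 (three centres), age 1, STRONGkids 1 (assuming two categories), PIM2 1, PELOD 1, and diagnosis 4 to 13. The SAP does not define the diagnosis groups. Five groups is an assumption; fourteen is the number of randomisation strata (protocol 18.2).
- 1+2+1+4+1+1+1 = 11
- 1+2+1+13+1+1+1 = 20

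**2. The protocol's own power figure.** A two-proportion z-test with 720 per arm, 20% against 15% and alpha 0.05 gives 80.3% one-sided and 70.5% two-sided. Protocol 15.4 states 80% and 70%, so the method reproduces its figures.

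**3. Anchor for deaths.** Protocol 15.4 says a 2-point mortality change "can be excluded with a power of around 62-75% depending on the true mortality in the total population". I solved for the overall mortality p, with arms at p plus and minus 1 point:

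power = Φ(0.02 / √[(p₁q₁ + p₂q₂)/720] − z)

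- 75% power: p = 2.1% (two-sided) or 2.8% (one-sided).
- 62% power: p = 2.9% (two-sided) or 3.9% (one-sided).
- Check at p = 2.1%, two-sided: √[(0.0300 + 0.0109)/720] = 0.00754; 0.02/0.00754 − 1.96 = 0.69; Φ = 0.755.

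Subgroup size: the SAP Background says "undernutrition in children who are admitted to the Pediatric Intensive Care Unit (PICU) is up to 24" per cent, so at most 0.24 × 1440 ≈ 346 children. Then 346 × 2.1% ≈ 7 and 346 × 3.9% ≈ 14 deaths of any timing. Deaths by day 7 are only part of these, and 24% is an upper bound; the Background's link between undernutrition and mortality pushes the other way. I used 5, 10 and 17. The range is 5/20 = 0.25 to 17/11 = 1.5 deaths per coefficient.

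**4. Simulation within the subgroup.** 346 children, 1000 datasets per setting, 5 or 14 diagnosis groups. Assumptions:
- Centre shares 45/45/10%; one diagnosis group 40%, the rest equal; high STRONGkids 20%.
- Log-odds 0.7 per SD PIM2, 0.4 per SD PELOD, −0.3 per SD age, 0.3 for STRONGkids, 0/0.2/0.3 for centre, −0.5 to 0.8 across diagnoses.

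Both fits use the same covariates. Firth maximises ℓ(β) + ½ log|I(β)|. A maximum-likelihood treatment coefficient above 6 in absolute value counts as inestimable and is dropped; Firth is scored on every dataset, which favours the SAP model. Root mean squared error of the log odds ratio (ranges span 5 to 14 groups):

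| Deaths | True OR | SAP model | Firth | SAP mean log-OR (true value) |
|---|---|---|---|---|
| 5 | 1 | 1.19-1.64 | 0.83-0.88 | −0.03 to 0.05 (0) |
| 5 | 2 | 1.15-1.51 | 0.84-0.94 | 0.61-0.63 (0.69) |
| 10 | 1 | 0.84-1.08 | 0.66-0.68 | −0.03 to 0.05 (0) |
| 10 | 2 | 0.89-1.02 | 0.75-0.79 | 0.75-0.84 (0.69) |
| 17 | 1 | 0.66-0.71 | 0.54-0.56 | −0.03 to 0.05 (0) |
| 17 | 2 | 0.65-0.77 | 0.55-0.57 | 0.77-0.85 (0.69) |

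Excess error is 22-98% at 5 deaths, 13-59% at 10 and 18-35% at 17. Scoring both methods only on datasets where maximum likelihood gives an estimate, a repeat run gave 18-71% at 10-17 deaths, with mean log-OR 0.80-0.92 at OR 2.

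Inestimable at 5 deaths: 15-23% (OR 1) and 23-28% (OR 2), of which 13-15 and 20-21 points are all deaths in one arm. At 10 deaths it is 1-5%; at 17, none.

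**5. Inference.** Coverage is 93-100% for the SAP model's Wald interval and 94-98% for Firth's profile interval. Rejection at OR 1 is 0-7% and 2-6%. Power at OR 2 lies between 11% and 14% for both at 10 deaths, and between 23% and 25% at 17.

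**6. Whole-cohort alternative.** Fitting all 1440 children with a treatment-by-undernutrition term and the same covariates by both methods gave 8-18% excess error at 10-17 deaths in one run and 14-25% in another; at 5 deaths it was 18-30%.

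**7. Sensitivity.** With stronger covariate effects, 20 coefficients and 10 deaths, the error ratio reached 1.97. By median absolute error it was 1.19-1.56 across all 10-death settings.

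**The case against.** The strongest reply is that the key input is missing. No document gives the subgroup's size or deaths, 17 lies above the 7-14 anchor, and 346 rests on an upper-bound prevalence. That stands: sparsity is plausible, not shown.

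The model is also partly inferred. The covariate list is attached to time-to-event outcomes; carrying it over is the natural reading but is not stated. The planned interaction tests need both nutritional groups in one model, and if the subgroup effect is taken from there the gap is much smaller. The SAP's sample-size sentence, which refers to the number of undernourished children, makes a separate fit plausible without specifying it.

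A reader might infer that the mortality test is invalid or that covariates make the model collapse. Neither follows. Coverage and type I error are acceptable, the chi-square test remains, there is no bias at OR 1 and no exaggeration at 5 deaths, and most failures come from one-arm deaths. In the 5-death runs the covariates add only 2 points (5 groups) to 8 points (14 groups).

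Firth is not the only remedy. Ordinary maximum likelihood on treatment, PIM2 and PELOD alone had error 0.81-0.84, 0.73-0.78 and 0.54-0.63 at 5, 10 and 17 deaths, so fewer covariates give much of the gain; but that drops centre and diagnosis, which define the randomisation strata. Finally, maximum likelihood has no finite mean squared error under separation, so the percentages depend on how failed fits are handled. They are orders of size, not constants.

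**Conclusion.** The point holds as a modest, cheap improvement to one adjusted estimate of a secondary safety outcome. Given 10-17 deaths and a fit within undernourished children, the planned model costs roughly 15-70% in error against Firth on the same covariates. At a true OR of 2 its mean log odds ratio is 0.75-0.92, that is, an OR of e^0.75 = 2.1 to e^0.92 = 2.5. Under a whole-cohort interaction model the excess error is about 8-25%. At about 5 deaths the excess is larger and the estimate is sometimes missing.

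This rests on an assumed death count, subgroup size, number of diagnosis groups and covariate strength. It does not extend to infections or durations. Nor do the documents show that hypoglycaemia or 90-day mortality is sparse, and the latter is more naturally a Cox outcome. Intervals will be wide under either method.

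**What to change.** Add to the SAP, Statistical analyses: for 7-day mortality, and for any other binary safety outcome with 20 or fewer events among undernourished children, fit the adjusted model with the same covariates by Firth-penalised logistic regression, with a profile-likelihood 95% interval. The threshold is a fixed event count, not tied to the number of coefficients. Beside the planned chi-square test, report the unadjusted risk difference with a score 95% interval, which exists even when all deaths fall in one arm; in simulation the Newcombe form had 94-98% coverage and a width of 6-10 percentage points. Leave infections and durations as planned.

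The cost is a few lines of text and standard software; centre and diagnosis stay in the model. The downside is shrinkage toward no effect, which matters for a safety outcome. At a true log odds ratio of 0.69 the mean Firth estimate is 0.49-0.57 at 5 deaths, 0.63-0.66 at 10 and 0.67 at 17, so it is mainly an issue at about 5 deaths and should be stated with the result.

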## **Aims and hypotheses**

The aim of this secondary analysis is to investigate the clinical effect of late PN in children who were undernourished upon admission, and to investigate the prognostic value of change in weight during PICU stay and the effect of late PN hereon. Furthermore, we will analyze the impact of Late PN on the relation between weight change and clinical outcome in relation to undernourishment upon admission, if the number of patients in each group is sufficiently large.

We hypothesize that undernourished children who have been allocated to the late PN group will have less new infections and a shorter duration of PICU stay than those allocated to the early PN group. Furthermore, in line with previous findings, we expect that weight deterioration is associated with worse clinical outcome. We expect that there is no difference in weight change between children receiving early PN and those receiving late PN, and that the relation between weight change and clinical outcome is not affected by late PN.

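### The SAP's weight-change analyses adjust for admission malnourishment, apparently as a yes/no term, where the continuous admission SD score is available and would control confounding much better

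*Supplement*

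**What the plan says.** All references are to the SAP.

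- **Data collection and definitions.** Nutritional status rests on the WFA SD score in children under one year and the BFA SD score in older children. "Acute undernutrition is defined as WFA or BFA SD scores" below -2. Belgian and Canadian patients are excluded from the analyses of weight change, so these use the Dutch patients only; their number is not given.
- **Statistical analyses.** "Change in weight will be reported as change in WFA or BFA SD score", so the change is kept on the continuous scale. For the baseline: "Analyses regarding change in weight will additionally be adjusted for malnourishment upon admission". This comes on top of centre, age, diagnosis group, STRONGkids category, PIM2 and PELOD. No continuous admission SD score is named in any model.
- **Aims and hypotheses.** One aim is the prognostic value of weight change during the PICU stay, with deterioration expected to go with worse outcome. Another is the effect of late PN on weight change. A third is "to investigate the clinical effect of late PN in children who were undernourished upon admission".
- **Background.** Undernutrition on admission is described as associated with higher mortality and morbidity. The only prevalence given comes from the literature: "The prevalence of undernutrition in children who are admitted to the Pediatric Intensive Care Unit (PICU) is up to 24" per cent.

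**The concern.** Change is discharge score minus admission score, so the admission score is built into it. Unless the two are perfectly correlated, children who start low tend to drift up and children who start high tend to drift down. If children who start low also do worse, as the Background suggests, the admission score confounds the association between weight change and outcome.

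A yes/no term removes only the difference between the two group means. Within each group a child at -2.1 and one at -4 are treated alike, as are a child at -1.9 and one at +1, and the confounding continues there.

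The direction matters for the SAP's own hypothesis. Low starters gain and do worse, so what is left of the confounding works against the expected finding that weight loss goes with worse outcome. A weak or null prognostic result could then come partly from the adjustment.

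**Working it through.** **The plan's own figures.** The SAP gives no number for this point. The one design figure that can be checked is the parent trial's power (final protocol, 15.4) for infections of 20% versus 15% with 720 per arm. A pooled-variance two-proportion calculation gives 80.3% one-sided and 70.5% two-sided, against the stated 80% and 70%. It reproduces, but nothing below rests on it.

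**Inputs**
- Cut at -2: SAP, Data collection and definitions.
- Share below the cut, p: 24% is the literature maximum in the Background. The trial's own share is not given, so 5-24% is an assumed range.
- Roughly normal score, linear effects, equal spread at admission and discharge, and an admission-discharge correlation r of 0.80-0.95: all assumed.

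**Step 1. How much of the score the indicator captures.** For a normal score cut so that a share p lies below, the share of its variance captured is φ(z_p)² / [p(1 − p)].

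At p = 0.24: z = −0.706, φ = 0.311, and 0.311² / (0.24 × 0.76) = 0.0967 / 0.1824 = 0.53. So 53% is captured and a share u = 0.47 is left.

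**Step 2. Bias that remains when change predicts outcome.** Let b be the admission score's own effect on outcome per SD-score unit.
- With no baseline adjustment, the change coefficient is biased by −b × (1 − r) / [2(1 − r)] = −0.50 b.
- After adjusting for the indicator, the bias is −b × u / [(1 − r)u + (1 + r)].
  - r = 0.80: 0.47 / (0.094 + 1.80) = 0.25 b, which is 50% of the unadjusted bias.
  - r = 0.95: 0.47 / (0.0235 + 1.95) = 0.24 b, which is 48%.
- After adjusting for the continuous score, the bias from this source is zero.

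A separate linear simulation (500,000 children; correlation between score and change of −0.3 or −0.5) gave:

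| Share below cut | Score variance not captured | Confounding left (simulation) | Left with an added covariate correlated 0.5 with the score |
|---|---|---|---|
| 24% | 47% | 51-54% | 45-48% |
| 15% | 57% | 61-64% | 52-56% |
| 10% | 66% | 69-72% | 58-61% |
| 5% | 78% | 80-82% | 65-68% |

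The last two columns are shares of the crude confounding. The added covariate stands in for something like STRONGkids category; its correlation is an assumption. With the continuous score, 0-3% was left, which is simulation noise.

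**Step 3. Could the sign reverse?** At p = 0.24 the remaining bias is 0.24-0.25 times b. To cancel the true effect of weight change, b would have to be 1/0.248 = 4.0 to 1/0.238 = 4.2 times that effect. At p = 0.10 the same formula gives a bias of 0.33-0.34 times b, hence a ratio of about 3. The documents give no size for either effect.

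**Step 4. The comparison of weight change between arms.** Randomisation removes confounding, so only precision is at stake. In units of the score's variance, the residual variance of change is (1 − r)²u + (1 − r²) with the indicator and 1 − r² with the continuous score.
- r = 0.80: 0.3788 versus 0.3600, a 5% reduction.
- r = 0.95: 0.0987 versus 0.0975, a 1% reduction.

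**The case against.** **The term may not be binary.** The SAP does not say so, and it defines undernutrition rather than malnourishment. That is fair. However, the below -2 rule is the only definition given, and the term is a condition rather than a score. If the authors meant something else, the SAP should say it.

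**Other covariates do some of the work.** STRONGkids category, age, diagnosis and the severity scores may carry part of the admission score. This stands in part: under the assumed correlation of 0.5 the remainder at 24% falls from 51-54% to 45-48%, so most of it stays.

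**The size is conditional.** 24% is a literature maximum, and normality and linearity are assumed. This stands, but a lower prevalence makes the remainder larger. The linear algebra is also only an approximation for the logistic and Cox models.

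**One slope across two measures.** The score is WFA under one year and BFA above it, with country-specific or WHO references. A single linear term may not fit both, so the fix needs a check on this.

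Three stronger readings may tempt a reader, and the documents do not support them.

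- *The estimate may be reversed.* This would need an admission-score effect about four times that of weight change at 24% prevalence. The Background says only that undernutrition is associated with worse outcome.
- *The between-arm comparison of weight change is biased.* It is randomised; the cost is a small loss of precision.
- *The cut also spoils the test of whether nutritional status modifies the late-PN effect, so that test should use the continuous score.* The stated aim is "to investigate the clinical effect of late PN in children who were undernourished upon admission", which needs a defined subgroup. The SAP gives a "threshold for significance of interaction set at" 0.10 or below but names no modifier, so use of the cut there is inferred. The power argument also depends on the shape of the effect. For a linear interaction with 80% power on the continuous score, the cut gives 55-57% at 24% prevalence. If the effect steps at -2, the cut does better (74% versus 46% in simulation). That is a trade-off and not an error.

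**Conclusion.** The point holds for the analyses in which weight change predicts outcome. On the natural reading, a yes/no term stands in for the change score's own baseline and leaves about half or more of the confounding by the admission score: roughly 47-54% at 24% undernourished, rising to about 80% at 5%, before any small reduction from the other covariates. The expected consequence is attenuation of the association between weight loss and worse outcome. For late PN versus early PN on weight change, the loss is about 1-5% of residual variance at 24% prevalence.

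The conclusion rests on four things: that malnourishment means a score below -2; a roughly normal score with linear effects; an assumed prevalence range, because the trial's own is not given; and, for the size of the bias per unit and the precision loss, an admission-discharge correlation of 0.80-0.95. The direction also needs low admission scores to go with worse outcome, which the Background supports.

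**What to change.** In the SAP's Statistical analyses, change the baseline term of the weight-change analyses to: *adjusted for the admission WFA/BFA SD score as a continuous variable, with a check for non-linearity (for example a spline) and for a difference between the WFA and BFA age groups.*

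Keep the effects in children below -2, and the interaction tests, as planned. A treatment-by-continuous-score interaction may be added as a supportive sensitivity analysis, not as a replacement.

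The cost is one sentence and one model term in place of another, plus a spline and an age-group term for the checks. The admission scores must already be computed to apply the cut, so no new data are needed.
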